## Abstract

**Rationale and Aim:** Infants with Congenital Heart Disease (CHD) are at risk for neurodevelopmental delays, emotional, social and behavioral difficulties. Hospitalization early in life and associated stressors may contribute to these challenges. Family-centered Care (FCC) is a health care approach that is respectful of and responsive to the needs and values of a family and has shown to be effective in improving health outcomes of premature infants, as well as the mental well-being of their parents. However, there is limited empirical data available on FCC practices in pediatric cardiology and associations with parent and infant outcomes.

**Methods and Analysis:** In this cross-sectional study, we will explore FCC practices at two pediatric cardiac intensive care units in Germany, assess parent satisfaction with FCC, and investigate associations with parental mental well-being and parenting stress, as well as infant physical and mental well-being. We will collect data of 280 infants with CHD and their families. Data will be analyzed using multivariate statistics and multilevel modeling.

**Implications and Dissemination:** The study protocol was approved by the medical ethics committees of both partner sites and registered with the German registry for clinical trials (NR DRKS00023964). This study serves as a first step to investigate FCC practices in a pediatric cardiology setting, providing insight into the relationship between FCC and parent and infant outcomes in a population of infants with CHD. Results will be disseminated in peer-reviewed journals.

## Introduction

Congenital Heart Disease (CHD) is defined as a structural anomaly of the heart or intrathoracic vessels present at birth (1). Incidence of CHD is reported at 9.41 per 1,000 live births worldwide (2). Advances in cardiovascular medicine and surgery have led to improved survival rates of patients with CHD in the past decennia, with an estimated 34.5% decline in mortality between 1990 and 2017 worldwide and an at least 60% decline in Western Europe (3). The majority of children born with CHD now reach adulthood, with a 10-year survival rate of over 80% (4). With this changing demographic, new challenges arise. Patients are confronted with long-term physical health problems, like arrhythmias or heart failure (5). Furthermore, neurodevelopmental delays are frequently observed throughout childhood, with implications for academic achievement, job and life satisfaction (6–8). The cause of these neurodevelopmental delays in this population is hypothesized to be multifactorial and characterized by complex pathways over time (9). Brain dysmaturation, frequently observed in infants with CHD, is suggested as a risk factor, making them neurologically vulnerable to a myriad of stressors early in life, particularly during hospitalization due to open-heart surgery (10). A recent review on the psychosocial development of infants with CHD shows that they are also at risk for emotional, behavioral, and social difficulties (11). The authors hypothesize that hospitalization may overwhelm an infant's capacity to regulate stress, causing these difficulties. Hospitalization is associated with various stressors, for instance invasive procedures, limited mobility, sensory overstimulation, a disrupted parent-infant relationship, or neurotoxic medication. The hospital environment may therefore be an important target for interventions to improve the developmental and psychosocial outcome in this population. A compelling approach to advance the infant's healthcare ecosystem to be more developmentally supportive is Family-Centered Care (FCC), which may promote infant health irrespective of the medical condition (12, 13).

FCC is an international standard of holistic care provision and defined as a health care approach that is respectful of and responsive to the needs and values of a family (14). According to the Institute for Patient- and Family-Centered Care, it comprises four main concepts: (I) respect and dignity, (II) information sharing, (III) participation in care and decision- making and (IV) collaboration between patients, families and the health-care team (www.ipfcc.org). In pediatric care settings, FCC acknowledges the family as the child's primary source of emotional, social and developmental support, and, importantly, as part of the health-care team (15). Accordingly, FCC is a value-based approach that comprises any specific measures and care practices that fall into line with above-mentioned principles. Concrete examples are rooming-in, educating parents/legal guardians, participation of parents/legal guardians in interdisciplinary team rounds, or their presence during medical procedures. Current guidelines for the neonatal, pediatric, and adult Intensive Care Unit (ICU) specify recommendations in the areas of family presence, family support, communication with family members, consultations with specific professional groups, and operational and environmental issues, with varying degrees of scientific evidence (14). Importantly, the endorsement of FCC by professional associations and political institutions is lacking in Europe. The European Foundation for the Care of Newborn Infants has formulated a European Standard of Care for Newborn Health, but it has not been formally implemented in Germany or other European countries. Nevertheless, some of the recommendations may be informally realized in clinical practice. While the evaluation of FCC, by using validated parent satisfaction and experience questionnaires, is implemented as part of a national quality benchmarking tool in the Netherlands, we are not aware of other European countries who routinely evaluate FCC (16). A prospective survey conducted at neonatal intensive care units in Finland, Sweden, Norway, Estonia, Spain and Italy found that FCC practices vary substantially between units with regards to family presence and perceived quality (17).

Most studies on the effects of FCC practices on various physical and mental health outcomes have been conducted with premature infants and their families in neonatal intensive care units, with favorable results. Ding and colleagues recently published a review and meta-analysis of 19 randomized controlled trials investigating the effects of FCC interventions pertaining to educational support, personalized care, parent support, information/communication and environment (18). Results show that FCC interventions improve the clinical outcome of the infant, i.e., weight gain and readmission rates. Above that, these interventions also improve parent-reported outcomes, i.e., satisfaction with care, stress and symptoms of anxiety and depression, which in turn may have an effect on child physical and mental well-being (19).

The holistic nature of the FCC approach aims at minimizing stressors and maximizing a developmentally supporting environment centered on the family-system and falls into line with current insights into child development (20). Accordingly, FCC should be beneficial to various at-risk populations, with potentially lasting effects on both physical health (via immune function and inflammatory processes), and mental well-being (21). Melnyk and colleagues conducted a randomized controlled trial on FCC in a heterogeneous pediatric patient cohort (22). They investigated the effectiveness of an educational-behavioral intervention in mothers of 2- to 7-year old children submitted to a pediatric intensive care unit for various reasons (e.g., respiratory problems, infections, and cardiac problems). The intervention reduced parenting stress levels during hospitalization. Furthermore, similarly to studies in premature babies, the intervention improved maternal mood and reduced symptoms of anxiety and depression. Above that, the intervention had an effect on child mental well-being, specifically externalizing symptoms- a result that warrants further research (22). The results of this study supports the notion that the beneficial effects of FCC may extend to various medical cohorts. In pediatric cardiology, several authors argue that FCC practices may be applicable to infants with CHD, pointing to a mismatch between the neurobiological needs of these infants and the hospital environment (23–29). The neurological vulnerability observed in infants with CHD resembles that of premature infants, most notably with regard to white matter immaturity (30). Two studies investigating in-hospital caregiving interventions for parents of premature infants found positive effects of the intervention on frontal EEG power and cerebral white matter maturation and connectivity of the infant, supporting the notion that a positive early environment stimulates neurodevelopment in this vulnerable group (31, 32). Providing FCC to hospitalized infants with CHD may be similarly beneficial to neurodevelopment and thus improve short-term and long-term outcomes. However, to our knowledge, there is limited empirical support that demonstrates the effectiveness of FCC in this specific population and no studies have been conducted on FCC practices at Pediatric Cardiac Intensive Care Units (PCICUs) caring for children with CHD in Germany.

Primary aim of this cross-sectional two-center study is to investigate FCC practices at two PCICUs in Germany. As infants are limited in their ability to verbalize their needs and experiences during hospital stay, assessing the experiences of parents is crucial for the evaluation of the quality of care (33). We will compare the two participating centers concerning parent satisfaction with FCC and unit adherence to FCC practices in hypothesis generating analyses.

Secondary aim of the study is investigating associations between parent satisfaction with FCC practices and parent, as well as infant outcomes. On the parent level, we hypothesize that higher parent satisfaction with FCC is associated with lower levels of parental anxiety, depression, stress, and parenting stress, similarly to the findings on FCC interventions in premature babies. Accordingly, we will investigate these associations in hypothesis confirming analyses. On the child level, we will investigate associations between parent satisfaction with FCC and child mental and physical well-being as rated by the parents. The analysis will be hypothesis generating, as there is minimal prior research to guide hypotheses about parent satisfaction with FCC and infant mental well-being, and as associations between parent satisfaction with FCC and infant physical well-being may be specific to the underlying medical condition.

## Methods and Analysis

### Design

This two-center cross-sectional study will be conducted at two PCICUs of two specialized pediatric cardiac centers in Germany (Berlin, Bad Oeynhausen).

### Study and Outcome Measures

#### Socio-Demographic Information

Socio-demographic information of the primary caregiver will be assessed with a purpose-designed questionnaire based on German demographic standards (34). The questionnaire comprises questions about age, migration background, first and second language, educational and professional background, current employment status, legal and partnership status of the primary caregiver, as well as number, age and gender of children.

#### Unit Adherence to FCC Practices

We will use the Gap Analysis Tool provided by the Society of Critical Care Medicine (SCCM) Guidelines for Family-Centered Care in the ICU (35). This tool comprises all 24 recommendations of the guidelines by the SCCM, which are rated to indicate how frequently the ward already implements each recommendation as follows: 0 (nearly always), 1 (usually), 5 (sometimes), 10 (nearly never). For recommendations only applicable to neonatal ICUs, a “not applicable” option is available. Each score is transferred into an item score by multiplying the frequency score by outcome points, which are specified for each recommendation. Outcome points range from 1 to 5 depending on the importance of the particular outcome the recommendation targets. Accordingly, item scores range from 0 to 50.

#### Parent Satisfaction With FCC Practices

We will use the EMpowerment of PArents in The Intensive Care-30 Questionnaire (EMPATHIC-30) (36). It is a self-report instrument consisting of 30 statements and assesses satisfaction with experiences at the ICU. The questionnaire is divided into five domains: information (five items), care and cure (eight items), parental participation (six items), organization (five items) and professional attitude (six items). Responses are given on a six-point scoring scale ranging from 1 (“certainly no”) to 6 (“certainly yes”). A separate box “not applicable” is available for all statements. The questionnaire was translated and culturally adapted for use in German-speaking populations by Nagl-Cupal and Lippoldt (37). Latour and colleagues reported a Cronbach's a of 0.93 on the full scale and Cronbach's a ranging from 0.73 to 0.81 on the domain level (36).

#### Complexity of Disease

##### Classification of CHD Severity

We will classify CHD severity according to three diagnostic categories proposed by Warnes and colleagues (38): complex (e.g., truncus arteriosus/hemitruncus, transposition of the great arteries), moderate (e.g., coarction of the aorta, tetralogy of Fallot), and mild (e.g., isolated small ventricular septal defect without associated lesions, isolated congenital aortic valve disease).

##### Aristotle Comprehensive Complexity Score

We will assess the complexity of cardiac disease using the Aristotle Comprehensive Complexity score (ACC) (39). This pediatric risk score is based on expert opinion and ranges from 1.5 to 25. It consists of three dimensions (complexity, procedure-dependent factors, and procedure-independent factors), each comprising several factors, which in turn comprise several variables (three variables for the complexity dimension, 167 for the procedure-dependent factors, and 81 for the procedure-independent factors). Each variable has a reference value that was created by asking medical professionals to score each variable regarding their contribution to mortality, morbidity and difficulty on a scale from 1 to 5, and by computing the median of the scores. The Aristotle Comprehensive Complexity Score predicted 30-day mortality and length of ICU stay during the 1st postoperative week as well as morbidity after congenital heart surgery in previous studies (40, 41).

#### Infant Physical and Emotional Well-Being

We will use the German Version of the Pediatric Quality of Life Inventory [PEDSQL, (42)] to assess both infant physical and emotional well-being as rated by the parents. The acute version for infants aged 1–12 months consists of 36 items and assesses infant well-being within the past seven days. It comprises five subscales (physical functioning, physical symptoms, emotional functioning, social functioning and cognitive functioning). For the assessment of parent-rated physical well-being, we will use the physical health summary score, which consists of the subscales physical functioning (six items) and physical symptoms (10 items). For parent-rated mental well-being, we will use the emotional functioning subscale (12 items). Responses are given on a five-point scale ranging from 0 (“never”) to 4 (“almost always”). The PEDSQL for infants has good internal consistency reliability, with a Cronbach's a of 0.92 for the total scale scores and Cronbach's a of 0.82 and 0.87 for the physical health summary score and the emotional functioning subscale, respectively (42).

#### Parent Emotional Well-Being

We will use the German version of the Depression Anxiety Stress Scale (DASS-21) in order to measure symptoms of depression, anxiety and stress of the parents (43, 44). It is a self-report instrument consisting of 21 items and assesses negative emotional states within the past 7 days. It comprises three subscales with seven items each: depression, anxiety and stress. Responses are given on a four-point scoring scale ranging from 0 (“not at all”) to 3 (“most of the time”). The scale has good internal consistency reliability, with Cronbach's a of 0.90, 0.81, and 0.86, for the subscales depression, anxiety and stress, respectively (45).

#### Parenting Stress

We will assess parenting stress by using the German version of the Parental Stressor Scale: Neonatal Intensive Care Unit [PSS:NICU, (46)]. The German version of the scale consists of 13 items and assesses the extent of stress caused by experiences in the ICU. It comprises two subscales: infant behavior and appearance, and parental role alterations. The third subscale was removed due to a low number of items and unclear factor structure in the German psychometric study. Responses are given on a five-point scale ranging from 1 (“not at all stressful”) to 5 (“extremely stressful”). The scale has good internal consistency reliability, with Cronbach's a of 0.85 for the full scale and Cronbach's a of 0.82 and 0.87 for the subscales infant behavior and appearance, and parental role alterations, respectively (47).

### Participants

Participants will be infants aged 0–12 months, hospitalized for treatment of CHD at one of the two pediatric cardiac centers, and their primary caregiver. The attending physician will recruit participating families during their hospital stay at the participating PCICU. Participation is voluntary.

#### Inclusion Criteria

- Infant is diagnosed with congenital heart disease- Infant is aged 0–12 months at recruitment- Hospitalization at the PCICU for ≥12 h- Primary caregiver has German language proficiency.

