### Procedure

At commencement of data collection, the senior physician and senior nurse of each participating PCICU will fill out the Gap Analysis Tool. All parents of infants hospitalized with CHD will be recruited after discharge from the PCICU, upon admission to the normal/intermediary care unit. The attending physician of the intermediary/normal care unit will check inclusion and exclusion criteria and provide oral and written study information to eligible parents. If parents decide to participate, the attending physician will obtain written informed consent from all parents with custody rights. The attending physician will then assess primary caregiver status by asking who took over most caregiving responsibilities (e.g., feeding, bathing, changing diapers) for the child during the past month. The primary caregiver will then receive the questionnaires and a return envelope. They will be asked to complete the questionnaires within 24 h after discharge from PCICU and hand it to one of the staff members of the unit in the sealed envelope, to ensure confidentiality. One of the investigators at each site will collect the returned questionnaires and hand them to a member of the research team not involved in the clinical care for the patients, for data entry. The principal investigator at each site will document the patient characteristics (infant age, gender) and medical information (e.g., diagnoses, duration of stay at PCICU, room size at PCICU) for each participating infant.

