##### Secondary Analyses

In order to investigate associations between parent satisfaction with FCC practices and parent, as well as infant outcomes, we will use multilevel models with PCICU as the level two factor. Such models account for shared exposure to unit characteristics, causing families within a unit to be more similar (to an unknown extent) compared to families from different units.

For the analysis of outcomes on the parent level, we will enter parent satisfaction with FCC as independent variable. Measures of parent well-being (specifically, symptoms of anxiety, depression, stress and parenting stress) will be entered as dependent variables. Extended models will be built to account for potential effects of infant characteristics (e.g., age and gender), medical variables (e.g., duration of stay at hospital, complexity of disease), as well as socio-demographic variables (e.g., employment status, ethnicity or professional background).

For each measure of parent well-being (symptoms of anxiety, depression, stress and parenting stress), a series of multilevel models is estimated. Each model in the set has incremental complexity. All models will be estimated using Restricted Maximum Likelihood, defining the covariance structure through variance components, and using the Huber- White sandwich estimator for the standard errors (50, 51).

For *each* parent well-being measure separately, the series of hypothesis confirming models is outlined below:

1) Model 1 estimates the unconditional means model for the parent well-being score.2) Model 2 estimates the conditional means model, adjusting for infant characteristics, medical and socio-demographic variables.3) Model 3 estimates the random intercept for the fixed slope association between FCC satisfaction and parent well-being, adjusted for infant characteristics, medical and socio-demographic characteristics.4) Model 4 estimates the random intercept and random slope for the association between FCC satisfaction and parent well-being, adjusted for infant characteristics, medical and socio-demographic characteristics.

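### DASS-21 and PEDSQL look back 7 days while a PCICU stay may last only 12 h, so for stays under about 2.5 to 3.5 days most of the outcome window precedes the care being rated

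*Protocol article*

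**What the plan says.** All references are to the protocol article.

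- **Eligibility (Inclusion Criteria):** "Hospitalization at the PCICU for ≥12 h". No longer minimum is set.
- **Timing (Procedure):** "They will be asked to complete the questionnaires within 24 h after discharge from PCICU".
- **Predictor (Parent Satisfaction With FCC Practices):** EMPATHIC-30 "assesses satisfaction with experiences at the ICU".
- **Parent distress (Parent Emotional Well-Being):** DASS-21 "assesses negative emotional states within the past 7 days", with subscales for depression, anxiety and stress.
- **Infant outcomes (Infant Physical and Emotional Well-Being):** the PEDSQL acute version "assesses infant well-being within the past seven days".
- **Parenting stress (Parenting Stress):** PSS:NICU "assesses the extent of stress caused by experiences in the ICU".
- **Models (Secondary Analyses):** "For the analysis of outcomes on the parent level, we will enter parent satisfaction with FCC as independent variable". The child-level models use the same predictor. Parent-level models are confirmatory and child-level models hypothesis generating. Hospital stay is named as an example covariate. The Procedure section, by contrast, has PCICU duration recorded for each infant.

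**The concern.** Predictor and outcome refer to different periods. EMPATHIC-30 and PSS:NICU are tied to the ICU experience, however long it was. DASS-21 and PEDSQL are tied to a fixed 7 days that ends at completion. After a long stay the two periods largely coincide. After a short one, most of the outcome period was spent elsewhere, before the rated care began.

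The secondary aim asks how satisfaction with PCICU care relates to parent and infant well-being, and the parent-level hypothesis is drawn from findings on FCC interventions. In short-stay families, an association between EMPATHIC-30 and a mostly pre-admission DASS-21 score is a different quantity: it may reflect how earlier mood colours a later rating. The described models estimate an FCC slope across all stays. The random slope in Model 4 varies by PCICU, not by length of stay. Adjusting for stay as an ordinary covariate shifts the outcome level but does not realign the two periods, and the covariate named is hospital stay rather than PCICU stay.

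**Working it through.** The article gives no figure for the overlap of the two periods, so there is none to reproduce on this point. Its nearest figure, the ANOVA minimum detectable effect of d = 0.34 at N = 2 × 140, does reproduce (noncentral t: power 0.809 at d = 0.34; minimum d = 0.336), but nothing below depends on it.

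**Inputs**

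- Recall window W = 7 × 24 = 168 h (DASS-21 and PEDSQL sections).
- PCICU stay s, at least 12 h (Inclusion Criteria). The distribution of s is not given, so 12 h to 168 h is used as a range.
- Time from PCICU discharge to completion g, from 0 to 24 h (Procedure).
- Assumption: one continuous PCICU stay.

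**Formulas**

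- PCICU share = min(s, W − g)/W
- Pre-admission share = max(0, W − g − s)/W
- Remainder = g/W, time after PCICU discharge (at most 24/168 = 14.3%)

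**Worked case, s = 12 h**

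- PCICU share = 12/168 = 7.1%.
- Pre-admission share at g = 24: (168 − 24 − 12)/168 = 132/168 = 78.6%.
- Pre-admission share at g = 0: (168 − 12)/168 = 156/168 = 92.9%.

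**Range**

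| PCICU stay | PCICU share | Pre-admission share, g = 24 h | Pre-admission share, g = 0 h |
|---|---|---|---|
| 12 h | 7.1% | 78.6% | 92.9% |
| 24 h | 14.3% | 71.4% | 85.7% |
| 48 h | 28.6% | 57.1% | 71.4% |
| 72 h | 42.9% | 42.9% | 57.1% |
| 96 h | 57.1% | 28.6% | 42.9% |
| 168 h | 85.7% to 100% | 0% | 0% |

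**Where the pre-admission part becomes the majority**

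W − g − s > W/2 gives s < 84 − g. That is s < 84 h (3.5 days) for completion at discharge and s < 60 h (2.5 days) for completion at 24 h. Families are approached only after PCICU discharge, so g = 0 is a limiting case and the practical threshold lies below 84 h.

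**Where the PCICU part becomes the majority**

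s/W > 1/2 gives s > 84 h. Four days (96 h, 57.1%) is the first whole number of days that meets this at any completion time up to 24 h.

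**Outcomes affected**

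Affected are the three DASS-21 subscales, out of four confirmatory parent outcomes, and the two PEDSQL outcomes. PSS:NICU asks about the ICU itself and is not affected.

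**The case against.** - **Reach is unknown.** Twelve hours is an eligibility floor, not a typical stay, and nothing in the article shows that short stays are common. If nearly all stays exceed about 3.5 days, the effect on the results is small. This stands, and it limits the point.
- **The aim is associational.** The Discussion says that the design cannot establish cause and effect. That limits how an association is interpreted. It does not settle which period the association concerns, so the mismatch remains. Mood colouring a simultaneous rating is a general limit of the design in families of every stay length; what is particular to short stays is that the outcome period itself mostly predates the care.
- **This is analysis-plan detail in a condensed article.** The covariates are given as examples and their functional form is not stated, so it cannot be said that stay will enter only additively. But the eligibility floor, the recall windows and the completion time are all fixed in the text, and the mismatch follows from them.
- **A loss of power.** A reader might shrink the slope in proportion to the overlap and report reduced power. The documents do not support this. It needs the scales to average evenly over the 7 days and only PCICU days to respond to FCC, and neither is stated. It is also tempting to start from 80% power at d = 0.34, but that is the ANOVA figure; for the multilevel models the article gives 74% at that effect.
- **A threshold of 4 days.** A reader might say that most of the window precedes admission for any stay under 4 days. That counts the hours after PCICU discharge as pre-admission. At 96 h only 28.6% to 42.9% precedes it.
- **Stay length is not a neutral divider.** Overlap is almost a function of PCICU stay, which plausibly tracks disease complexity. A slope extrapolated to full overlap would describe the longest-stay families and could differ because of severity. This stands, and it is why an interaction cannot be the main remedy.

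**Conclusion.** The mismatch follows from the article's own figures. For PCICU stays shorter than 60 to 84 h, more than half of the DASS-21 and PEDSQL window precedes PCICU admission, rising to 79% to 93% at the 12 h minimum. In those families the FCC slope largely relates a pre-PCICU state to a later rating of the PCICU. The thresholds rest on the stated recall windows and completion time and on a single continuous stay.

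A reader might infer that the confirmatory DASS-21 analyses cannot answer the secondary aim at all. The documents do not support that: the share of short-stay families is not given, so neither the size nor the direction of the net distortion in the pooled slope can be computed. The point is a cheap improvement to the interpretability of three confirmatory and two hypothesis-generating outcomes, not a flaw that invalidates the design.

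**What to change.** Keep the planned pooled models and add the following for the DASS-21 and PEDSQL outcomes, before the data are analysed.

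1. Pre-specify a sensitivity analysis restricted to families with at least 4 PCICU days, taken from the recorded PCICU duration and adjusted for disease complexity.
2. Use PCICU duration as the stay covariate, alongside or instead of hospital duration.
3. Report the interaction of FCC satisfaction with PCICU duration (or overlap share) as exploratory only, noting its confounding with severity.
4. State that, if the restricted and pooled slopes differ, the pooled slope will not be read as an association with distress or infant well-being during PCICU care.

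PSS:NICU needs no change, and neither do eligibility, instruments or sample size.

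**Cost:** PCICU duration is already collected, so items 1 and 2 need no new data. Using overlap share in item 3 would need the PCICU discharge and questionnaire completion dates. The main downside is lower precision: the restricted analysis drops an unknown part of a sample that the article already calls the maximum achievable.
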